### Eligibility

#### Inclusion criteria

To be eligible individuals must be: (a) Haitian, Hispanic, or Black, (b) report not having had appropriate screening for at least one of the following HIV, HCV, CRC, and cervical cancer (as per 2017 United States Preventive Services Task Force (USPSTF) guidelines: never had a HIV test; never had a HCV test; not had a colonoscopy in last 10 years and/or stool-based test in the last year; and not had a Pap smear within the past 3 years), and (c) age 50–65 years. Each preventive test has different age and other eligibility criteria. For example, cervical cancer screening is recommended for women ages 21–65, CRC is recommended from ages 50–75, and HCV is recommended for persons born between the years of 1945 and 1965. After consultation with our community partners, we selected this simplified age criterion (50–65 years), which maximizes the number of tests for which participants would be potentially eligible (three for men, four for women).

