#### Intervention Group 1—CHW-delivered navigation to primary care (PC) for disease screening

For participants assigned to Group 1, CHWs work closely with their FQHC supervisor to develop tailored navigation approaches appropriate for each person (consistent with the pragmatic trial design). First, they contact participants to assess which preventive services they are eligible for using a checklist based on the above criteria. For participants who already have a primary care provider (PCP), CHWs encourage such persons to follow up with their provider for needed tests. If they do not have a PCP or prefer not to go to their PCP for such testing, the preferred approach is to navigate participants to primary care services at local FQHCs where providers as part of routine care evaluate patients for needed preventive services. CHWs emphasize that while they are following a broad set of screening guidelines, only a PCP will know which preventive services are needed for each person based on their unique circumstance and risk profiles. As health center outreach workers, CHWs do not limit the scope of work to the four screening services. They also help link study subjects with other services offered by the centers (e.g. facilitated enrollment in health insurance plans, immigrant and refugee programs, behavioral health, and programs for people with diabetes), as needed. Participants may also prefer to obtain these services from other locations such as Project Screen (free cervical cancer screening for women age > 50), locations providing anonymous HIV and HCV testing, or health fairs sponsored by health centers or the University of Miami. In the third year of the study, the University of Miami began a separate, community-based cancer screening program using a mobile van that offers these screening services for free. On average, the vehicle goes to each of these communities at least once a month. Thus, we included the mobile van as an additional screening referral option for study participants in this group.

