#### Secondary outcomes

As a secondary study outcome, we will examine each screening individually as a binary variable and look at the change in screening completion from baseline to 6-month follow-up in each arm of the study. For example, change in proportion of people up to date in screening for HCV in each arm. Another secondary outcome we will consider is the increase in median number of screenings done. For this endpoint, the possible ranges will be 0 to 4 for women (HIV, HCV, HPV, FIT) and 0 to 3 for men (HIV, HCV, FIT).

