### Sample size calculation

The baseline screening rates in our sample size calculation rates are obtained from our feasibility studies and local data. The overall sample size was chosen to ensure sufficient power to detect clinically meaningful effects associated with a 15% point increase in proportion of additional screening done in the home-based arm versus primary care arm using two-sided test for differences in proportion. Although we plan to conduct intention-to-treat analyses, in which all women lost to follow-up will be considered “unscreened,” we will also conduct analyses with lost to follow-up participants excluded. For these analyses, we need to account for attrition (21% in our previous study). In addition, in our subgroup analysis where we look at each individual test, we set alpha at 1.25% instead of 5% to account for multiple testing. Even with a 25% attrition rate, a proposed total sample size of 900 participants (450 per arm and 150 per site) will give us over 95% power for our primary outcome and 90% power for the subgroup analysis.

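### The screening count is summarised by its median, which is too coarse to show a 15-point gain reliably; the same passage should also state the between-arm contrast and name its items by condition

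*Protocol article*

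**What the plan says.** Secondary outcomes in the Protocol article sets two endpoints.

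- **Single tests.** Each screening is a binary variable, and the plan will "look at the change in screening completion from baseline to 6-month follow-up in each arm of the study". The HCV example that follows is also worded per arm.
- **Count.** "Another secondary outcome we will consider is the increase in median number of screenings done". No between-arm contrast is attached to the median. The scale is spelled out by sex and by item, namely "the possible ranges will be 0 to 4 for women (HIV, HCV, HPV, FIT) and 0 to 3 for men (HIV, HCV, FIT").

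Three other sections bear on these.

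- Sample size calculation rests on a "15% point increase in proportion of additional screening done in the home-based arm versus primary care arm", with a two-sided test of proportions. It sets alpha at 1.25% for each individual test and claims 90% power there with 25% attrition.
- Inclusion criteria describe a person who is overdue as one who has "not had a colonoscopy in last 10 years and/or stool-based test in the last year; and not had a Pap smear within the past 3" (counted in years), so colonoscopy and Pap smear count as screening at entry.
- The Group 1 section says the preferred approach, for those without a provider or not wishing to use theirs, is to "navigate participants to primary care services at local FQHCs where providers as part of routine care evaluate patients for needed preventive services".

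**The concern.** The median of a count with four or five possible values carries little information. If the middle participant in each arm falls on the same integer, the reported difference is zero, however many others gained a test. If the middle participant sits near a step, the median jumps by a whole test although the mean moved by about half of one. What a reader is told about the count would then depend on where the base rate happens to lie, not on the intervention.

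Two smaller faults sit in the same passage. Change described arm by arm does not by itself compare the arms: people enter overdue for at least one test and both arms receive active help from community health workers, so both can be expected to rise. And the item list names HPV and FIT, which are the home-arm tests, while the entry criteria also recognise Pap smear and colonoscopy, which routine care may use in Group 1.

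**Working it through.** **Plan's own power figures.** Inputs from Sample size calculation: 450 per arm, 25% attrition, 15-point difference, alpha 5% (primary) and 1.25% (single tests). 450 × 0.75 = 337.5, taken as 337 per arm. No control rate is given, so I use the worst case, 42.5% versus 57.5%.

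Power = Φ[(0.15 − z·√(2·0.5·0.5/n)) / √(2·0.425·0.575/n)]. With n = 337 the two square roots are 0.0385 and 0.0381.
- Alpha 5% (z = 1.960): Φ(1.96) = 97.5%; the plan says over 95%.
- Alpha 1.25% (z = 2.498): Φ(1.41) = 92.1%; the plan says 90%.

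Both claims are met when all 337 contribute. The cervical test applies to women only, and the article gives no share of women, so I do not extend the 92.1% to it.

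**Median, exact calculation.** Assume independent tests with equal rates, and women with four tests.
- 40% to 55%: the cumulative probability at 1 and 2 tests is 0.475 and 0.821 before, 0.242 and 0.609 after. The median is 2 in both cases. The mean goes from 4 × 0.40 = 1.6 to 4 × 0.55 = 2.2, a rise of 0.60.
- 30% to 45%: the cumulative probability at 1 test is 0.652 before and 0.391 after. The median goes from 1 to 2. The mean again rises by 0.60.

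The same effect is shown as zero or as one whole test. For men the mean shift is 3 × 0.15 = 0.45. Over control rates of 5% to 80%, a 15-point gain in every test leaves the median unchanged for about 31% of rates (women only), 40% (men only) and 43% (50–60% women, pooled).

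**Median, simulation.** Assumed: 337 per arm, half women, each test overdue with probability 0.5, 0.7 or 1.0, control completion 0.25, 0.35 or 0.45, completion 15 points higher in the home arm, within-person correlation 0.3. The count was taken both as new tests done and as tests up to date.
- Arm medians were equal in about 94–99% of trials in several scenarios and near 0% in others.
- A rank test at 5% had at least 91% power throughout.

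**Per-arm change.** If 30% of 337 gain a test in each arm and none lose one, the within-arm McNemar statistic is √(337 × 0.30) ≈ 10 in both arms, with no difference between them.

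**Item list read literally.** Assume true completion of 45% in both arms, and that 25% of screened Group 1 participants had a Pap smear or colonoscopy instead. Credited Group 1 completion is 0.45 × 0.75 = 33.75%, a false home-arm advantage of 11.25 points. With 337 per arm at alpha 1.25% this would be declared significant about 69% of the time. With shares of 10% and 50% the false difference is 4.5 and 22.5 points.

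**Restricting to the overdue.** If 70% are overdue, 337 × 0.70 ≈ 236 per arm. The power formula at alpha 1.25% then gives Φ(0.77) ≈ 78% if the effect stays at 15 points.

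**The case against.** **The median.** The plan says only that it will consider this outcome. It drives no sample size, and the test may be left to an analysis plan not shown. A rank test could accompany a reported median, and by the figures above it would have ample power. Separate ranges are given for women and men, so pooling is not stated. All this is fair, and it limits the weight of the point. But the article does fix the summary as the increase in the median, and the coarseness appears within each sex as well as pooled.

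**Per-arm change.** A reader might infer that the single tests have no between-arm comparison. The documents do not support that. Sample size calculation ties each test to home-based versus primary care, with its own alpha and power, and Statistical analysis plans regression models that include study arm. What remains is a conflict of wording.

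**Item list.** A reader might infer that Pap smears and colonoscopies in Group 1 will score zero, or that an HPV self-sample cannot make a woman up to date. Neither is established. HIV and HCV are conditions, so the list mixes labels and is plausibly shorthand. Primary outcome and Secondary outcomes speak of being up to date by condition. The Group 1 section accepts many screening sites, and the Discussion's worry about over-reporting in that arm presupposes that routine-care screening counts. The Pap wording is an entry rule, and the Group 2 sections treat self-sampling as cervical screening. What stands is an ambiguity, which under the literal reading of the count would favour the home arm.

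**Conclusion.** The point holds for the median. On a 0–4 or 0–3 scale it can hide a 15-point gain in every test almost completely, or show it as a full step, depending on base rates the article does not give. The 94–99% figure belongs to some assumed scenarios only and is not a prediction for this trial. A mean or rank comparison does not have this weakness.

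The per-arm wording and the HPV/FIT labels are matters to reconcile, not evidence of a missing comparison or a biased count. The false difference of 11.25 points rests on an assumed modality share and on the literal reading. The primary outcome names no test and is not touched. No sample-size figure is shown to be wrong here. This is a worthwhile correction to secondary endpoints and does not threaten the trial's main conclusion.

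**What to change.** Reword Secondary outcomes in one edit.

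1. **Count.** Compare the arms at 6 months by the difference in mean number of screenings, or in the proportion of needed screenings completed, with a 95% confidence interval, and test with a Wilcoxon test stratified by site and gender. Drop the median as the summary.
2. **Single tests.** State each as home-based versus primary care at 6 months, matching Sample size calculation. Keep all randomised participants to whom the test applies in the main comparison. An analysis of those overdue at baseline can be added as supportive. Its worst-case power is about 78% if 70% are overdue and the effect stays at 15 points; a larger effect among the overdue would offset this.
3. **Items.** Label them HIV, HCV, cervical and CRC, and list the accepted tests once, identically for both arms.

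The cost is the rewording and matching coding of the 6-month data. No visits or participants are added. With enrolment well advanced, the change should be dated and made before outcomes are examined by arm.

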### Statistical analysis

Prior to any analysis, data screening for accuracy will be conducted and will focus on several aspects. We will determine the amount, pattern, and randomness of missing data. Outliers will be identified observations that appear to be very high or very low, and decide how to proceed based on the presumed cause. We will also identify inconsistencies within a single variable and between variables. As there are various types of measurements, we will use various descriptive statistics to visualize the study data with the appropriate graphical displays. Initially, we will perform an explanatory data analysis; visually via graphics/plots such as scatter and box-whisker plots and numerically by descriptive statistics such as range, median, means, standard deviations for measurements taken on a continuous scale, and percentages, various types of cross-tabulations for measurements taken on a categorical scale. Corresponding confidence intervals for means and proportions will also be calculated. To have a better understanding of the relationships among different study measurements, parametric or non-parametric correlation coefficients, bivariate, and multidimensional cross-tabulations, scatter and box-whisker plots will be constructed. Prior to analyses, baseline differences of key covariates from the PC and HBT arm will be examined with respect to our primary and secondary outcomes, particularly those related to race, ethnicity, SES and education. We will also examine differences on key variables between subjects who completed the study and those lost to follow-up. Our primary analysis will consist of chi-squared testing for the differences in proportions among the PC versus HBT study arms. Several univariate and multivariate logistic regression models will be used to calculate odds ratios and corresponding 95% confidence intervals for exploring the result of the screening and the relation to various types of key study variables in addition to study arms. Two-way interaction terms between for various study variables and the study arms may need to be included in the models. Transformations of the continuous data in order to meet statistical assumptions may be undertaken if indicated. Type-1 error will be set to 5% (α = 0.05) for calculating confidence intervals and testing various hypotheses for the primary outcome. Adjustment of type-I error for multiple comparisons will be performed by controlling the family-wise type-I error rate at the 0.05 level. Standard diagnostic tools will be used to assess any model fit. All statistical analyses will be carried out using SAS® v9.4 for Windows (SAS Institute, Cary, NC, USA) and/or R-project for Windows.

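### The secondary count of screenings is summarised by the increase in its median, which on a 0–4 or 0–3 scale can be 0 or 1 for the same effect

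*Protocol article*

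**What the plan says.** The Secondary outcomes section of the protocol article names two kinds of secondary outcome. Each screening is analysed on its own as a binary variable, as a change from baseline to 6 months in each arm. The second is a count: "Another secondary outcome we will consider is the increase in median number of screenings done". Its scale is set by sex: "the possible ranges will be 0 to 4 for women (HIV, HCV, HPV, FIT) and 0 to 3 for men (HIV, HCV, FIT".

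The section gives no other summary for the count. It does not say whether the increase is between arms or from baseline within an arm, or whether women and men are combined. The Statistical analysis section names chi-squared tests and logistic regression for the outcomes, and medians and means only as general descriptive statistics.

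Two other places bear on the point. The Sample size calculation ties a clinically meaningful effect to a "15% point increase in proportion of additional screening done in the home-based arm versus primary care arm". The Inclusion criteria admit people who "report not having had appropriate screening for at least one of the following" of the four conditions, so the number of tests a participant needs can differ within each sex.

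**The concern.** The median of an integer count with four or five possible values is itself nearly always an integer. It stays put until the cumulative proportion at some integer crosses 50%, and then moves by a whole unit. Whether an effect shows depends on where the base rate lies relative to those crossing points.

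The trial asks whether several home tests can be delivered together. The primary outcome answers this as all or nothing, and the single-test outcomes answer it one test at a time. The count is the only measure that grades how many tests a person completed. Reported as a change in median, it could read as no change beside a real gain on every test. It could also read as 1 to 2, which looks like a doubling, for a gain of the same size.

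**Working it through.** **Inputs.** From the Sample size calculation: a 15-point gain, 450 per arm and 25% attrition. From Secondary outcomes: the 0–4 and 0–3 scales. The article gives no base rates, so the control-arm completion rate per test is assumed and ranged. The main case also assumes independent tests with equal rates and the 15-point gain on each test.

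**1. The plan's own figure.** No power is stated for the count. The power stated for the proportions reproduces. With 0.75 × 450 ≈ 337 per arm and the least favourable pair, 42.5% vs 57.5%:
- Null SE = √(2 × 0.25/337) = 0.0385; alternative SE = √(2 × 0.425 × 0.575/337) = 0.0381.
- At two-sided α = 0.05: (0.15 − 1.960 × 0.0385)/0.0381 gives 97.5% power, against over 95% stated.
- At α = 0.0125: (0.15 − 2.498 × 0.0385)/0.0381 gives 92.1%, against 90% stated.

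**2. Exact medians.** The count is Bin(4, p) in women and Bin(3, p) in men. The median is the smallest m with P(X ≤ m) ≥ 0.5.

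| Sex | p | P(X ≤ 1) | P(X ≤ 2) | Median |
|---|---|---|---|---|
| Women | 30% | 0.652 | 0.916 | 1 |
| Women | 45% | 0.391 | 0.759 | 2 |
| Women | 40% | 0.475 | 0.821 | 2 |
| Women | 55% | 0.241 | 0.609 | 2 |
| Men | 30% | 0.784 | 0.973 | 1 |
| Men | 45% | 0.575 | 0.909 | 1 |
| Men | 40% | 0.648 | 0.936 | 1 |
| Men | 55% | 0.425 | 0.834 | 2 |

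In the median, 30% vs 45% is +1 for women and 0 for men; 40% vs 55% is 0 for women and +1 for men.

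**3. How often.** Control rates 10% to 80% in steps of 5 points give 15 settings.
- Women: equal medians at 20, 40, 45 and 65%, so 4 of 15.
- Men: equal at 25, 30, 35, 55, 60 and 80%, so 6 of 15.
- Sexes pooled, with 50, 60 or 70% women: 20 of 45.

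**4. Sensitivity.** On a fine grid of base rates from 0 to 85%, the medians are equal for about 29% of rates in women and 47% in men.
- With 25% lost and scored 0: 36% and 50%.
- With correlated tests (beta-binomial, correlation 0.1 to 0.5): 28–33% and 46%. At correlation 0.5, about 5% of base rates in women give a change of 2.

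**5. The mean.** The expected difference is the sum of the gains: 4 × 0.15 = 0.60 tests for women and 3 × 0.15 = 0.45 for men. Neither the base rate nor correlation between tests changes it.

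**6. Simulated trials.** With 168 per arm in one sex (half of 337, an assumed even split) and 500 replicates, women at 40% vs 55% showed an observed median difference of 0 in 74% of trials and of 1 in 21%. Men at 30% vs 45% showed 0 in 98%. In the same trials a rank-sum test and a comparison of means were each significant in over 99%.

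**The case against.** The best defence is that little hangs on this. The outcome is secondary, is introduced as something to be considered, and carries no power claim. If every test rose by 15 points, equal medians would stand beside well-powered gains on the individual tests. The article names a summary and no test, and an analysis plan not shown may pair it with a rank test, which would detect the effect. This limits the importance of the point. It does not remove it, because a rank test repairs the p-value and not the effect measure that the article states.

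Several stronger readings are tempting and do not hold:
- *That no other endpoint shows joint completion.* The primary outcome, being up to date on all needed screenings, does. The count is only the sole graded measure.
- *That the sexes are pooled.* The article gives separate ranges and does not say they are combined. With 60% women pooled, 40% vs 55% gives medians 1 and 2 while 45% vs 60% gives 2 and 2. Within sex that contrast vanishes: at both base rates women are 2 and 2 and men 1 and 2. The defect within sex appears at other base rates.
- *That the endpoint is plainly a between-arm difference.* The wording also allows a rise from baseline. The median is equally coarse either way, though the binomial table is then only illustrative, since entry requires at least one overdue test.
- *That the median discards a signal of about 7 standard errors.* That is the pooled mean difference of 0.54 tests with 337 per arm under independence. With correlation of 0.3 to 0.5 it falls to about 5.5 to 4.8.

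**Conclusion.** The point holds as a weakness in a stated effect measure. For one and the same 15-point gain on every test, the median changes by 0 or 1 according to the base rate, with no change in 4 of 15 assumed settings for women and 6 of 15 for men. The mean difference stays at 0.60 and 0.45.

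These counts rest on assumed base rates and, in the main case, on independent tests with equal rates. The pattern survives correlation and loss scored as zero. Because the article gives no base rates, a reader might infer but cannot conclude that this trial will show a zero median change. Nor do the documents support a claim that the trial as a whole could miss a benefit: the primary outcome, the single-test outcomes and their power are unaffected. The number of tests needed may vary within sex, but the article does not give its distribution, so no figure can be put on that. The change is worth making, at the level of a secondary outcome.

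**What to change.** In Secondary outcomes, make the effect measure the between-arm difference in the mean number of screenings done by 6 months, with a 95% confidence interval, stratified by or adjusted for sex and site, and for the number of tests needed at intake. Show the distribution of the count by arm and sex, and report the median descriptively only.

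The share of needed tests completed may be added as a separate measure. It is not equivalent to the mean count when people need different numbers of tests: the count gives more weight to those who need more, and the individual share does not.

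The cost is a small change to the summary measure of one secondary outcome and a few lines of analysis code. No new data are needed.

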#### Intervention Group 2—CHW-delivered, home-based testing (HBT)

The CHWs develop tailored approaches appropriate for each participant in Group 2. First, CHWs use a checklist (as described above) to help determine which screening tests are needed. Participants in Group 2 are offered home-based testing. For these participants, there are various strategies CHWs may use. First, the CHW and the participant select a place of mutual agreement to conduct the needed screenings. Most typically, it will be at the participant’s home, although it can be at another community location. At the intervention visit the CHWs perform HCV and HIV screenings and provide post-test counselling. For the cervical cancer screening, they instruct participants how to do human papilloma virus (HPV) self-sampling. Participants are offered HPV self-sampling at the intervention visit, and typically provide the self-collected specimen to the CHW during the intervention visit. If for some reason the participant cannot complete the HPV self-sampling during the intervention visit, the CHWs will leave the kit with the participant and the participant can send the sample via mail. Persons needing a fecal immunochemical test (FIT) receive instruction on how to do the test and are given the kits, which they mail back. For mailed kits, the CHWs conduct follow-up phone calls encouraging participants to mail the kits back (FIT, HPV). CHWs also call participants with the results of the home-based testing, and, if needed, do home visits for post-test counselling. All participants who elect to do home-based testing also receive a letter explaining their results which they can provide PCPs. All participants who elect to do home-based testing are still urged to follow-up with a PCP for routine primary care. CHWs explain to participants that the PCP can not only review the letter describing the tests the CHW provided to the participants but also assess for other additional screening tests or follow-up treatments the participants may need.

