### Outcome measures

#### Primary outcome

Our primary study outcome measure will be proportion of participants fully up to date on all their needed screenings for these four health conditions (three for men) at 6 months post-study enrollment. We will conduct intention-to-treat analysis based on study allocation. This outcome will be a binary (yes/no) variable. Participants in either group lost to follow-up at 6 months will be assumed not to have been screened in intention-to-treat analyses.

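### The number-of-screenings endpoint names only the home-arm tests for cervical and colorectal cancer, while the entry criteria name Pap smear, colonoscopy and stool test; one arm-neutral list is needed

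*Protocol article*

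**What the plan says.** All references are to the protocol article.

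- **Inclusion criteria.** Lack of appropriate screening is described test by test. For HIV and HCV: "never had a HIV test; never had a HCV test". For CRC: "not had a colonoscopy in last 10 years and/or stool-based test in the last year". For cervical cancer: "not had a Pap smear within the past 3 years". No HPV test is named.
- **Intervention Group 1 (PC).** Community health workers (CHWs) "assess which preventive services they are eligible for using a checklist based on the above criteria". The tests themselves come from the participant's provider, a health centre or another venue. No cervical or CRC test is named for this arm.
- **Intervention Group 2 (HBT).** The same tool is used: "CHWs use a checklist (as described above) to help determine which screening tests are needed". For cervical cancer, "they instruct participants how to do human papilloma virus (HPV) self-sampling"; for CRC, participants receive a FIT kit.
- **Primary outcome.** The "proportion of participants fully up to date on all their needed screenings for these four health conditions (three for men"), at 6 months, scored yes or no. No qualifying tests are listed.
- **Secondary outcomes.** Each screening is analysed as a change from baseline to 6 months. A further endpoint is the increase in the median number of screenings, for which "the possible ranges will be 0 to 4 for women (HIV, HCV, HPV, FIT) and 0 to 3 for men (HIV, HCV, FIT".

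**The concern.** The two arms receive different tests by design. HBT supplies HPV self-sampling and FIT; PC supplies whatever the provider or venue offers. A list that names only one arm's tests can therefore misclassify participants differently by arm, and randomisation does not protect against that.

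The count endpoint names HPV and FIT. Pap smear and colonoscopy, which the same article accepts as screening at entry, are missing from it. The endpoint is also an increase from baseline. If baseline status follows the entry criteria and follow-up follows the count list, part of the measured change is a switch of definition.

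At stake is the arm comparison on the count, and on any other outcome to which an analyst carries the same list.

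**Working it through.** **1. The plan's own figure.** The article gives no figure on this point. The nearest is its power statement: 900 participants, 25% attrition, a 15-point difference. That leaves 900 × 0.75 / 2 ≈ 337 per arm. The control rate is not given, so I assumed 10% to 70%. The least favourable pair is 42.5% vs 57.5%. With pooled variance, power = Φ{[0.15 − z·√(2·0.5·0.5/337)] / √[(0.425·0.575 + 0.575·0.425)/337]}:
- two-sided α = 5%: (0.15 − 1.96 × 0.0385) / 0.0381 = 1.96, power 97.5%;
- two-sided α = 1.25%: (0.15 − 2.50 × 0.0385) / 0.0381 = 1.41, power 92.1%, for a test that applies to all participants.

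The stated power of over 95% and of 90% reproduces. Sample size is not the issue here.

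**2. The lists side by side.**

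| Condition | Entry criteria | HBT delivers | PC delivers | Count endpoint |
|---|---|---|---|---|
| HIV | any previous test | oral swab test | not specified | HIV |
| HCV | any previous test | finger-stick test | not specified | HCV |
| Cervical | Pap smear, 3 years | HPV self-sample | provider's choice | HPV |
| CRC | colonoscopy, 10 years, and/or stool test, 1 year | FIT | provider's choice | FIT |

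HIV and HCV agree throughout. The conflict is confined to cervical cancer and CRC.

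**3. The count applied as written.**
- HBT woman with HIV, HCV, HPV and FIT: 1 + 1 + 1 + 1 = 4 of 4.
- Woman screened for all four conditions with HIV, HCV, Pap smear and colonoscopy: 1 + 1 + 0 + 0 = 2 of 4.
- Man screened for all three with HIV, HCV and colonoscopy: 1 + 1 + 0 = 2 of 3.

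The loss falls only on people screened by Pap smear or colonoscopy, who are more likely to be in PC. The effect on the arm medians cannot be derived. It depends on the PC test mix, which is not given. A median of whole-number counts also moves in steps, so it may not move at all or may move by a full test.

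**4. Scale of the loss if the FIT-only label were carried to a CRC proportion (inputs assumed).** Let the true PC rate be 30% and s the share of that screening done by colonoscopy. Recorded rate = 0.30 × (1 − s). For s = 20%, 40% and 60% this gives 24%, 18% and 12%, a loss of 6, 12 and 18 points. Neither input is in the documents.

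**5. Why the composite should share the list (inputs assumed).** Take 50% women, true rates of 42.5% (PC) and 57.5% (HBT), and let q be the share of fully screened women in one arm whose only cervical test is not counted.
- Pap-only list: difference = 0.575 × (1 − 0.5q) − 0.425. For q = 0.25 it is 7.8 points; for q = 0.5, 0.6 points.
- HPV-only list: difference = 0.575 − 0.425 × (1 − 0.5q). For q = 0.25 it is 20.3 points; for q = 0.5, 25.6 points.

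The true difference is 15 points in each case. This shows how sensitive an all-or-nothing outcome is to the list. It is not an estimate for this trial.

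**6. The CRC wording.** Read as requiring that neither test was done, and/or accepts either test as sufficient. Read as requiring that at least one is missing, it makes both tests necessary, so FIT alone and colonoscopy alone both fail. Neither reading singles out an arm.

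**The case against.** The strongest reply is that the bracketed tests are shorthand explaining why the range is 0 to 4 for women and 0 to 3 for men, and that they belong to a single secondary endpoint. The entry criteria decide who enrols, not how outcomes are scored. Test-level scoring is usually left to a full protocol or analysis plan that is not shown.

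Much of this stands. Two stronger readings are tempting, and the documents support neither.

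- A reader might infer that the primary result changes sign according to which section is followed, or that HBT women screened by self-sample can never succeed. But the abstract, the aims and the Primary outcome section are all worded by condition. The Group 2 section and the section on the HPV self-sampling device treat self-sampling as cervical screening, and the Discussion plans to validate self-reports with home-test laboratory data. The checklist says which screenings are needed, not which test satisfies the need.
- A reader might infer that every rule penalises one arm's usual test. The CRC entry wording does not, and the article names no usual PC test; a health centre could use FIT or HPV testing.

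What does not fall away is that the article states a list for the count, and that list leaves out tests the same article accepts as screening. That is a stated rule in conflict with another, not detail left for later. If it is shorthand, replacing it costs nothing.

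**Conclusion.** The point holds for the count endpoint. As written, it credits the home-arm tests for cervical cancer and CRC and gives nothing for a Pap smear or colonoscopy. It also measures an increase from a baseline status described by different tests. The direction favours HBT, on the assumption that Pap smears and colonoscopies are commoner in PC, which follows from provider choice but is not stated. A person screened for everything can lose up to 2 of 4 points (women) or 1 of 3 (men). The effect on the arm comparison cannot be computed from the documents.

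For the primary composite the point is narrower. It is worded by condition and not directly governed by the list. However, the only definition of adequate screening available to it, in the Inclusion criteria, omits the HPV test that HBT delivers, so the sections need reconciling. The and/or wording for CRC is a separate ambiguity in eligibility and in which tests are needed, not an arm-specific bias.

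**What to change.** In Secondary outcomes, replace the bracketed tests by the four conditions (three for men), each satisfied by any listed test:

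- cervical cancer: Pap smear or HPV test, clinician- or self-collected;
- CRC: colonoscopy or stool-based test, overdue only if neither falls within its window;
- HIV and HCV: any test.

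Keep the look-back windows already stated and add one for the HPV test. Apply this single list in both arms, at baseline and at 6 months, and in the composite, the individual outcomes and the count. Reword the CRC entry criterion to match, so that and/or disappears.

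The cost is wording in the eligibility and outcome sections, plus a check that the intake and follow-up questionnaires ask about each test type. Care in either arm does not change.
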